## Methods and analysis

### Design

The Perforation EVents during ENdovascular Therapy for acute ischemic stroke (PREVENT) Registry is an international, multicenter, prospective, and retrospective observational study collecting data on vessel perforations during thrombectomy.

Data collection includes the following:

Patient baseline data (e.g., age, sex, pre-stroke modified Rankin Scale (mRS), pre-stroke anticoagulation or platelet therapy, and others).Data on the initial ischemic event (e.g., NIHSS at admission, number and location of vessel occlusions, TOAST classification [trial of ORG 10172 in Acute Stroke Treatment], imaging features related to clot composition, intracranial atherosclerotic disease (ICAD) or primary intracranial dissection, non-interventional stroke management, and other relevant factors).Details on circumstances and technique of the thrombectomy (e.g., anesthesiological management, type of aortic arch, cervical stenosis, thrombectomy technique, design and dimensions of the thrombectomy devices, operator experience, and others).Hemostatic therapy (e.g., non-endovascular hemostatic measures such as lowering of the systemic blood pressure or medication with coagulation effects, endovascular hemostatic measures including timing, exact mechanism, effectiveness, and other relevant factors).Outcome measures (e.g., functional outcomes including mRS at 90 days, and imaging outcomes including recanalization status, volume of intracranial hemorrhage, and other relevant factors).

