The collected data are stored safely in a REDCap database. Periprocedural imaging and the first postinterventional CT or MRI are obtained for the extraction of quantifiable imaging parameters, exploration of patterns, and quantification of the volume of extravasated blood and contrast agents. Imaging data are stored in a safe, password-protected Picture Archiving and Communication System (PACS) at Basel University Hospital, Basel, Switzerland. The duration of active intracranial bleeding is derived from the time stamps of the digital subtraction angiography series during thrombectomy displaying contrast extravasation. The collateral status will be derived from the first intraprocedural angiographic run. The flow rate of extravasation (i.e., the volume of extravasation per second) will be classified by the imaging core laboratory based on the first angiographic run that demonstrates extravasation. This will be used as a surrogate for perforation magnitude. A semi-quantitative assessment of the flow rate of extravasation will be sought, if technically feasible. Imaging evaluation will be carried out by a central imaging core laboratory to ensure a consistent interpretation.

PREVENT exclusively consists of data and imaging that have initially been collected for clinical purposes of patient care. As an observational study, PREVENT does not contain a randomization.

PREVENT aims to answer the following questions:

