### Data analysis

Summary tables for patient demographics as well as baseline and intervention characteristics will be provided. Further statistical analysis will be tailored for each of the study’s aims. The methods per aim are presented below, following the same order:

To identify risk factors associated with vessel perforations, we will, in the first stage, make comparisons between cases with and without perforation during thrombectomy for predefined risk factors. Statistical analyses will include paired samples *t*-test, Wilcoxon test, and chi-squared test or Fisher’s exact test. Furthermore, multivariable logistic regression models can be used to identify the association between multiple variables and the occurrence of vessel perforations.An exploratory analysis of the interventional image material in the central image analysis laboratory is planned. After reviewing the image material of approximately 20% of patients with explorative intention, imaging criteria will be defined with regard to possible mechanisms of vessel wall injury and distinct pathophysiological phenomena. These criteria will be used to classify the remaining 80% of patients. Due to the exploratory nature, no definitive statistical evaluation strategy can yet be determined.For this purpose, data-driven K-nearest neighbor clustering will be applied to identify different groups of similar patient characteristics. We will consider 2–4 clusters, and the distribution of the clusters will be inspected visually. After the identification of the clusters, we will compare the pathophysiological characteristics between the clusters.Patients with perforation will be divided into two groups: patients who received interventional hemostatic therapy after the perforation occurred—e.g., temporary intracranial balloon occlusion or permanent vessel occlusion with liquid embolization or coils—and patients who did not receive hemostatic therapy. Propensity score matching or inverse probability of treatment weighting will be used to control for the location of perforation and the flow rate of extravasation. The two groups will be compared with each other to identify differences in the duration of extravasation and in clinical outcomes. The appropriate statistical model will be used for each of the clinical outcomes (e.g., logistic regression model for binary outcomes and ordinal regression model for ordinal outcomes).Patients with perforation will be divided into two groups: patients in whom thrombectomy was continued after the perforation occurred and patients in whom the procedure was aborted. Propensity score matching or inverse probability of treatment weighting will be used to control for the amount of extravasation, stroke severity, occlusion location, collateral status, and other clinical outcome predictors. The two groups will be compared with each other to identify differences in clinical outcomes.The new insights on risk factors, mechanisms, and pathophysiology of vessel perforation will be gathered. An expert panel will discuss potential modifications to current thrombectomy workflows to reduce the risk of periprocedural perforation, both in response to specific patient-related risk factors (e.g., occlusion location and vessel tortuosity) and in general. No definitive statistical evaluation strategy can yet be determined.

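### Aim 4 names only two bleeding covariates for a non-randomised comparison of clinical outcomes, although aim 5 also controls for stroke severity, collateral status and other outcome predictors

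*Protocol article*

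**What the plan says.** The Data analysis section divides perforation cases, for aim 4, into those who did and did not receive interventional hemostatic therapy. Matching or weighting on a propensity score is to "control for the location of perforation and the flow rate of extravasation". The groups are then compared to "identify differences in the duration of extravasation and in clinical outcomes". On the outcome analysis the text adds: "The appropriate statistical model will be used for each of the clinical outcomes". It gives logistic and ordinal regression as examples and names no covariates.

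For aim 5 (thrombectomy continued versus aborted), the same section applies the same two techniques, again among perforation cases and for clinical outcomes. There they are to "control for the amount of extravasation, stroke severity, occlusion location, collateral status, and other clinical outcome predictors".

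The Design section states that the study is observational and not randomised. It lists among the collected data "age, sex, pre-stroke modified Rankin Scale (mRS), pre-stroke anticoagulation or platelet therapy, and others", "NIHSS at admission, number and location of vessel occlusions" and, as an outcome, "functional outcomes including mRS at 90 days". It also says: "The collateral status will be derived from the first intraprocedural angiographic run".

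**The concern.** Perforation location and flow rate describe the bleed. They do not describe the patient's prognosis apart from the bleed. Functional outcome at 90 days also depends on stroke severity, age, pre-stroke function and collaterals. If any of these also influences whether the operator treats the leak, the two groups differ in prognosis before hemostatic therapy starts. A propensity score built on location and flow rate removes that difference only as far as the factor is correlated with those two variables.

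The protocol recognises this problem in aim 5, where it controls for such predictors, but aim 4 gives no reason for a narrower set. The study questions in the Design section ask which patients with ongoing extravasation should receive endovascular hemostasis. The aim 4 estimate is therefore meant to inform treatment decisions, and a difference in prognosis could be read as benefit or harm of hemostatic therapy.

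**Working it through.** The documents give no effect size, power or outcome rate for aim 4, so there is no plan figure to reproduce. The check compares the covariate lists and then illustrates the possible size.

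**1. The lists side by side**

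| Factor | Aim 4 | Aim 5 | Collected (Design section) |
|---|---|---|---|
| Bleeding magnitude | flow rate | amount of extravasation | yes |
| Location | of perforation | of occlusion | yes |
| Stroke severity | not named | named | yes, NIHSS at admission |
| Collateral status | not named | named | yes, first angiographic run |
| Age, pre-stroke mRS, antithrombotics | not named | under the open clause, if counted as outcome predictors | yes |

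The first two rows partly mirror each other. The real gap is stroke severity, collateral status and the remaining outcome predictors.

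**2. Illustration by formula (all inputs are assumptions)**

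Take one omitted binary factor, severe stroke, and no true treatment effect. Let p_t and p_u be the proportions with severe stroke among treated and untreated patients. Assume P(good outcome) = 0.40 in milder stroke, and let OR_s be the odds ratio of severe stroke for good outcome.

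- P(good | severe) = p_s, where p_s/(1 − p_s) = OR_s × 0.40/0.60.
- P(good | treated) = p_t × p_s + (1 − p_t) × 0.40, and likewise for untreated with p_u.
- Spurious OR = odds(treated)/odds(untreated).

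Central case, p_t = 0.60, p_u = 0.45, OR_s = 0.3:

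- The odds of good outcome in severe stroke are 0.3 × 0.667 = 0.20, so p_s = 0.20/1.20 = 0.167.
- Treated: 0.60 × 0.167 + 0.40 × 0.40 = 0.260, odds 0.351.
- Untreated: 0.45 × 0.167 + 0.55 × 0.40 = 0.295, odds 0.418.
- Spurious OR = 0.351/0.418 = 0.84.

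Extremes of the grid:

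| p_t / p_u | OR_s | Good, treated | Good, untreated | Spurious OR |
|---|---|---|---|---|
| 0.55 / 0.45 | 0.5 | 0.318 | 0.333 | 0.93 |
| 0.65 / 0.40 | 0.2 | 0.216 | 0.287 | 0.69 |
| equal | any | equal | equal | 1.00 |

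The direction is also assumed. Exchanging p_t and p_u gives the reciprocals, about 1.07 to 1.46.

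**3. Illustration by simulation**

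Inverse probability weighting was simulated in 2,000,000 patients with a true null. Mortality was about 50%, the figure given in the Introduction. Severity was assumed independent of location and flow rate, and here more severe patients were treated less often.

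| Severity OR for treatment, per SD | Severity OR for death, per SD | OR for death, location and flow only | Risk difference | OR with severity added |
|---|---|---|---|---|
| 1.0 | 1.5 to 2.0 | 0.99 to 1.00 | about 0 | 0.99 to 1.00 |
| 0.80 | 1.5 | 0.93 | −1.9 points | 1.00 |
| 0.50 | 2.0 | 0.70 | −9.1 points | 1.00 |

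With an assumed 250 versus 250 split, the chance of a false p < 0.05 in the two biased rows is about 6% and 53%. This is an unweighted approximation that ignores the variance cost of weighting. The last column uses the true propensity score.

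**The case against.** **The article does not say that nothing else will be adjusted for.** It is a condensed text, and full covariate lists are commonly left to the full protocol or SAP. A reader might infer that further covariates are ruled out. The wording does not support that, because the outcome regressions neither list nor exclude any. But this is not mere silence. The article states a two-item set for aim 4 with no open clause, then a wider, open-ended set for aim 5. Followed as written, aim 4 would leave the other predictors uncontrolled.

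**Different exposures may need different covariates.** The section says that the analysis is tailored to each aim, and bleeding variables are natural drivers of the decision to treat a leak. This stands in part. A reader might infer that aims 4 and 5 contradict each other, or should give the same answer. They estimate effects of different treatments, so neither follows. For duration of extravasation the narrow set may be adequate. It does not explain why prognostic factors should be irrelevant to a comparison of clinical outcomes.

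**The size is assumed.** This stands fully. No document figure supports the imbalances or the severity odds ratios. If severity is correlated with location or flow rate, those variables would absorb part of the imbalance.

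**Conclusion.** The point holds for the clinical outcomes of aim 4. The stated adjustment set covers the bleed but not the patient's prognosis. Aim 5 shows that the protocol regards the missing predictors as relevant to the same kind of outcome among perforation cases.

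The harm is conditional. Under the assumed imbalances of 10 to 25 percentage points and severity odds ratios of 0.2 to 0.5, a null effect would appear as an OR of 0.93 to 0.69 for good outcome. It would be zero if severity, and likewise each other prognostic factor, had no influence on treatment choice.

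A reader might infer that the hemostasis estimate will be biased by a known amount or in a known direction, or that several omitted factors must add up. The documents support none of these: they give no data on who receives hemostatic therapy, and separate biases can offset as well as reinforce each other. Confidence is high for the contrast in the text and low for the magnitude. The change should be made before the analysis; it does not call the registry's design into question.

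**What to change.** For the clinical outcomes of aim 4, extend the propensity model, the outcome regression, or both, to predictors fixed before the perforation and already collected. Keep perforation location and first-run flow rate, and add at least NIHSS at admission, age, pre-stroke mRS, pre-stroke anticoagulation or antiplatelet therapy, occlusion location and collateral status. The two-variable set can stay for duration of extravasation. If the sponsor prefers the narrow set for clinical outcomes too, the text should give the reason.

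Reperfusion grade at the moment of perforation is left out of this list. The Design section records recanalization status as an outcome, and nothing shows that it is recorded at that moment, so adding it could require new image reading.

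The change needs no new data, only revised analysis wording. The statistical cost is that a richer propensity model may reduce overlap between the groups, or need weight truncation, among about 500 cases whose treated/untreated split is not known in advance. Placing some predictors in the outcome regression instead eases that.

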**Objectives:**

The primary objectives of this study are to (1) identify risk factors for vessel perforation, (2) explore the underlying pathophysiology, (3) develop a classification system for vessel perforations, (4) compare different hemostatic treatment strategies, (5) evaluate the impact of continuing versus aborting thrombectomy after perforation, and (6) propose a safety-optimized thrombectomy technique.

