Which risk factors are associated with the occurrence of vessel perforations during thrombectomy?Is it possible to identify distinct mechanisms of vessel perforation? Is it possible to describe pathophysiological phenomena associated with vessel perforation?Are there groups of perforations that can be distinguished in terms of risk profiles and the need for urgent complication management, on the basis of which a classification system can be created? If so, can a pathophysiological explanation be found for the differences between these groups?In patients with ongoing contrast extravasation, which individuals should receive endovascular therapy to achieve hemostasis? How do specific hemostatic strategies compare to others regarding efficacy and safety?In patients in whom ongoing contrast extravasation has stopped, should thrombectomy be continued, or should the procedure be aborted?Based on the insights gained from PREVENT, is it possible to design a safety-optimized thrombectomy technique that may be used if patient-related risk factors imply an increased risk of vessel perforation?

Figure 1 shows the aims of the PREVENT registry.

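### Aim 5 asks about patients whose extravasation has stopped but compares all perforations, and it leaves open when the adjusted amount of extravasation is measured

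*Protocol article*

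**What the plan says.** The Protocol article words aim 5 in three places.

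- Design, question 5: "In patients in whom ongoing contrast extravasation has stopped, should thrombectomy be continued, or should the procedure be aborted". The population is limited to patients whose bleeding has ceased on angiography.
- Abstract, Objectives: "evaluate the impact of continuing versus aborting thrombectomy after perforation". There is no condition on cessation.
- Data analysis, fifth item: patients with perforation are split into "patients in whom thrombectomy was continued after the perforation occurred and patients in whom the procedure was aborted". Propensity score matching or inverse probability weighting is to "control for the amount of extravasation, stroke severity, occlusion location, collateral status, and other clinical outcome predictors", and clinical outcomes are then compared. Again there is no condition on cessation. Neither cessation status nor hemostatic therapy is a named covariate, and no decision time is given.

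The Data analysis section says that its methods follow the order of the aims, so the fifth item is the analysis for question 5. Under Selection/treatment of subjects, a case needs extravasation in at least one angiography series; cessation is not an entry condition.

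On measurement, the Design section says "Periprocedural imaging and the first postinterventional CT or MRI are obtained", among other purposes for "quantification of the volume of extravasated blood and contrast agents". It separately describes a flow rate of extravasation, classified "based on the first angiographic run that demonstrates extravasation". Aim 4 adjusts for that flow rate; aim 5 names an amount instead. The listed outcomes include "imaging outcomes including recanalization status, volume of intracranial hemorrhage".

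**The concern.** There are two problems.

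**Population.** Question 5 makes sense once bleeding has stopped, when continuing and aborting are both options to be weighed. The planned comparison also admits patients who were still bleeding. Ongoing bleeding is a plausible reason to abort and a plausible cause of death. If it is neither an exclusion nor a covariate, it confounds the comparison, and aborting will tend to look worse than it is.

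**Adjustment.** Extravasation up to the decision is a confounder and belongs in the propensity model. Extravasation after the decision may be a consequence of it, and conditioning on that part would hide harm that continuing does through further bleeding. The article does not say which of the two it means.

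Aim 5 is one of six primary objectives and is meant to inform a decision in a complication with mortality of about 50%.

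**Working it through.** The article gives no effect size, power or group event rates for aim 5, so there is no planned figure to reproduce. The core of the check is the comparison of texts above. The calculations below show only whether the mechanisms can matter. Every input except the 50% mortality and the 500 cases is assumed.

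**1. Crude mixture, no true effect.** Overall mortality is 0.50 (Abstract and Introduction). Assume that a share f never stops bleeding, that 90% of these die, that all are aborted, and that the rest split evenly.

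- Mortality in the rest, which is also that of the continued group: m = (0.50 − 0.90f)/(1 − f)
- Mortality in the aborted group: a = [m(1 − f)/2 + 0.90f]/[(1 − f)/2 + f]
- Odds ratio of death, continued versus aborted: [m/(1 − m)]/[a/(1 − a)]

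| f | m | a | OR |
|---|---|---|---|
| 10% | 0.41/0.9 = 0.456 | 0.295/0.55 = 0.536 | 0.72 |
| 20% | 0.32/0.8 = 0.400 | 0.34/0.6 = 0.567 | 0.51 |
| 30% | 0.23/0.7 = 0.329 | 0.385/0.65 = 0.592 | 0.34 |

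These are unadjusted, so they do not describe the planned analysis.

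**2. With weighting, no true effect.** Simulation of 400,000 patients per scenario, with weights from a logistic propensity score. F is a standard normal flow rate and S = 1 if bleeding has stopped.

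- log-odds of S = logit(nominal share stopped) − 0.8F
- amount before the decision A0 = F + 0.5(1 − S) + 0.7 × noise
- log-odds of continuing (C = 1) = −1.0 + 1.5S − 0.5A0
- final amount A1 = A0 + dC + 0.8(1 − S) + 0.5 × noise
- log-odds of death = −0.6 + eC + 0.8A1 + 1.0(1 − S)

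With d = 0 and e = 0, the true difference is zero. Estimated mortality difference, continued minus aborted, in percentage points:

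| Nominal share stopped | All cases, weighted on A0 | All cases, weighted on A1 | All cases, weighted on A0 and S | Stopped only, weighted on A0 |
|---|---|---|---|---|
| 50% | −9.7 | −3.5 | 0.0 | +0.1 |
| 70% | −7.9 | −3.0 | +0.2 | +0.2 |
| 90% | −3.7 | −1.6 | 0.0 | +0.1 |

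Pooling without cessation status leaves bias on either reading of the amount. Restriction removes it, and so does adding cessation status to the weights.

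**3. Timing of the amount, stopped patients only.**

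- If the decision adds nothing to bleeding (d = 0, e = 0), weighting on the final amount gives +0.2, +0.2 and +0.1 points, which is no material bias.
- If continuing adds to bleeding (d = 0.5) and has an offsetting direct benefit (e = −0.4), the true net difference is 0.0. Weighting on A0 gives +0.2, 0.0 and +0.1. Weighting on the final amount gives −7.3, −7.5 and −7.7, because the harm through bleeding has been adjusted away.

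**4. Precision after restriction.** Assume mortality of 50% versus 40%, equal groups of n and a two-sided 5% test: power = Φ[(0.10 − 1.96·√(2 × 0.45 × 0.55/n))/√((0.25 + 0.24)/n)].

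| Share of the 500 cases entering | n per group | Power |
|---|---|---|
| 100% | 250 | 61% |
| 90% | 225 | 57% |
| 70% | 175 | 47% |
| 50% | 125 | 35% |

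**The case against.** The strongest reply is that the missing condition is condensation. The article ties each analysis to its question by order. Aim 4 shows the same shorthand: its question concerns ongoing extravasation, yet its analysis also opens with all patients with perforation. Exact analysis sets are commonly left to the full protocol or the statistical analysis plan, and the catch-all of other outcome predictors could take in cessation status. This stands as a caution about intent. It does not remove the inconsistency: the abstract's objective is unrestricted too, so the article carries two versions of aim 5, and its analysis text follows the one that differs from question 5.

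Three stronger readings are tempting, and the document does not support them.

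- **That the amount of extravasation is itself a result of the decision.** No measurement time is given. It could be the volume including the scan after the procedure, the first-run flow rate, or the volume up to the decision. The contrast with aim 4's wording favours the first. On the other two it is a proper and needed confounder. If bleeding has already stopped at the decision, much of the volume would precede it.
- **That the aborted group includes patients already recanalised, or whose target vessel was permanently occluded for hemostasis.** The article does not say how either is classified, and a procedure that has reached its goal is not naturally called aborted.
- **That weighting cannot work for want of overlap.** This follows only if all still-bleeding patients were aborted, which is an assumption in step 1. In the simulation, where overlap exists, adding cessation status was enough.

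**Conclusion.** The point holds in this form. Question 5 and its analysis define different populations, and the pooled comparison, with no cessation restriction or named adjustment, does not answer the question as posed. This part is firm on the text.

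Bias after weighting is plausible, but its size cannot be known from the article. About 4 to 10 points of false mortality difference arose when the weights used bleeding before the decision, and about 2 to 4 when they used the final amount. Both rest on the assumptions that still-bleeding patients are aborted more often and die more often. The crude odds ratios of 0.34 to 0.72 should not be read as the error of the planned analysis.

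The second part is conditional. The measurement time of the amount is not fixed. A volume that includes imaging after the procedure may contain bleeding that followed the decision and overlaps with the listed hemorrhage-volume outcome. In the assumed case where continuing adds to bleeding, this cost 7 to 8 points; where the decision adds nothing, it cost nothing material.

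**What to change.** Reconcile the abstract's objective, question 5 and the fifth item of Data analysis:

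- Make the main aim-5 analysis set the patients with an angiographic run showing that extravasation has stopped. Take that run as time zero and classify continued or aborted from there.
- State how patients with no remaining target occlusion, or with a permanently occluded target vessel, are classified. Report everyone left out descriptively.
- Replace the undated amount by extravasation measures fixed by time zero, for example the first-run flow rate and the bleeding duration up to time zero. Keep hemorrhage volume on imaging after the procedure as an outcome only.

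This defines an analysis set and its covariates; it implies no view on when a procedure should be continued.

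The time stamps of the angiography series are already used to derive bleeding duration, so much of what is needed is in hand. The cost is threefold. Fewer than 500 cases enter aim 5, with the loss of precision shown in step 4. Cases without a datable negative run drop out, and their number is unknown because imaging is routine and goes back to 2015. The core laboratory also has some added coding to do on images already collected.

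### The aim 5 propensity score adjusts for an amount of extravasation that is not fixed to a time before the continue/abort decision, so it may adjust away bleeding that follows from continuing

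*Protocol article*

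**What the plan says.** Under Data analysis, aim 5 divides perforation patients into "patients in whom thrombectomy was continued after the perforation occurred and patients in whom the procedure was aborted". The groups are compared on clinical outcomes after propensity score matching or inverse probability weighting, which is meant to "control for the amount of extravasation, stroke severity, occlusion location, collateral status, and other clinical outcome predictors". The same section describes aim 4 differently: there the adjustment is to "control for the location of perforation and the flow rate of extravasation".

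The Design section says how some of these quantities are obtained. Flow rate is classified "based on the first angiographic run that demonstrates extravasation", and "This will be used as a surrogate for perforation magnitude". Collateral status, which is also on the aim 5 list, comes from the first run of the procedure. For volume, the text says "Periprocedural imaging and the first postinterventional CT or MRI are obtained" for several purposes, one of which is "quantification of the volume of extravasated blood and contrast agents". The outcome list in the same section names "imaging outcomes including recanalization status, volume of intracranial hemorrhage, and other relevant factors".

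No sentence says which of these measures the aim 5 covariate is, or up to what moment it is read.

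**The concern.** The exposure in aim 5 is a decision taken during the procedure, after the perforation. A propensity score for that decision should hold only variables already settled when it is made. Extravasation before the decision is a confounder and belongs in the score. Bleeding after the decision may be a result of it. Balancing the groups on a total that includes later bleeding compares continued and aborted patients who ended with a similar bleed, so any effect of the decision that runs through bleeding drops out of the contrast.

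This matters because continuing versus aborting is one of the article's primary objectives, the complication carries a mortality of about 50%, and the article regards randomization as infeasible. The adjustment therefore carries the inference.

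**Working it through.** The article gives no figure for this comparison to reproduce. It states a target of 500 cases and 500 controls, with no effect size or power for aim 5. The check has three steps.

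**Step 1. Timing of the candidate measures (Design and Data analysis).**

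| Measure | Imaging it is read from | Timing relative to the decision | Role given |
|---|---|---|---|
| Flow rate | First run showing extravasation | Before | Aim 4 covariate |
| Collateral status | First run of the procedure | Before | Aim 5 covariate |
| Duration of bleeding | Time stamps of the angiography series showing extravasation | Not capped at the decision | Compared between groups in aim 4 |
| Extravasated volume | Periprocedural imaging and first CT or MRI afterwards (listed together) | Partly after | Not stated |
| Amount of extravasation | Not stated | Not stated | Aim 5 covariate |

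The aim 5 extravasation term is not anchored, although the article anchors flow rate and collateral status.

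**Step 2. What happens if the final amount is used.** A simulation with 400,000 patients per scenario; every parameter is an assumption.

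- Stroke severity S and pre-decision amount P: independent standard normal.
- Probability of continuing: expit(-0.7P - 0.2S), so larger bleeds are aborted more often.
- Final amount: A = P + gT + uU + 0.7e, where T = 1 if continued, and U and e are standard normal.
- Probability of poor outcome: expit(-0.1 + 0.8A + 0.5S + 0.8uU - bT).
- g is the bleeding added by continuing (in SDs of P), b a direct benefit of continuing on the log-odds scale, and u the strength of an unmeasured factor affecting both bleeding and outcome.
- Weights: 1/p if continued, 1/(1 - p) if aborted, with p from a logistic model.

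Risk difference, continued minus aborted:

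| g | b | u | Truth | Score with S and P | Score with S and A |
|---|---|---|---|---|---|
| 0.3 | 0 | 0 | +0.048 | +0.047 | 0.000 |
| 0.5 | 0 | 0 | +0.080 | +0.079 | -0.001 |
| 1.0 | 0 | 0 | +0.157 | +0.158 | 0.000 |
| 1.0 | 0.5 | 0 | +0.060 | +0.062 | -0.099 |
| 0 | 0 | 0 | 0.000 | -0.002 | -0.003 |
| 0 | 0 | 0.7 | 0.000 | +0.001 | +0.024 |
| -0.5 | 0 | 0 | -0.079 | -0.079 | 0.000 |

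Errors with the final amount in the score:

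- g = 0.5: -0.001 - 0.080 = -0.081, so the harm is hidden.
- g = 1.0, b = 0.5: -0.099 - 0.060 = -0.159, and the sign reverses.
- g = -0.5: 0.000 - (-0.079) = +0.079, so a benefit is hidden.
- g = 0, u = 0.7: +0.024, so continuing looks worse than it is.

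Simulation error is roughly sqrt(2 × 0.25/200,000) = 0.0016, so differences of 0.002 to 0.003 are noise.

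Leaving extravasation out is no remedy. With S alone the estimate is -0.023 where the truth is +0.080 (g = 0.5), and -0.105 where the truth is 0 (g = 0, u = 0).

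**Step 3. Size against precision.** The article gives no split between continued and aborted patients. At a risk of 50%, the standard error of a risk difference is sqrt(2 × 0.25/n) for n per group: 0.045 with 250 per group (all 500 cases, split evenly) and 0.071 with 100 per group. The g = 0.5 error is then 0.081/0.045 = 1.8 or 0.081/0.071 = 1.1 standard errors.

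**The case against.** The strongest reply is that the article never says the aim 5 covariate is a postprocedural volume. The Design section lists its imaging sources and purposes together without pairing them, and the hemorrhage outcome has a different name. Flow rate is itself defined as a volume per second and serves as the surrogate for perforation magnitude, so the amount could mean flow rate, or flow rate combined with duration. The article's list of questions also poses this one for patients whose extravasation has already stopped; extravasation up to that point would be a proper confounder.

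Much of this stands. Equating the covariate with the postprocedural volume is an inference. It does not remove the point, for three reasons. Aim 5 uses a different term from aim 4 within one section, which makes a simple restatement of flow rate the less natural reading. A product of flow rate and duration would still need a cut-off, because duration is read from the whole procedure. And Data analysis does not carry over the restriction to patients whose bleeding has stopped.

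Two stronger readings are tempting and not supported. A reader might infer that continuing will look safer than it is. That requires continuing to add bleeding, which the article does not state; the table shows the bias vanishing or reversing otherwise. A reader might also infer that the open-ended reference to other outcome predictors lets final recanalization into the score. The article lists recanalization as an outcome, nothing proposes it as a covariate, and a full covariate list may properly be left to the analysis plan.

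The simulation is also favorable to the remedy, since the pre-decision amount is measured without error and, with severity, is the only confounder.

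**Conclusion.** The point holds in conditional form. Aim 5 names a covariate without tying it to a time before the decision, and the closest measure in the article draws partly on later imaging and overlaps a listed outcome. As worded, the score can contain a consequence of the exposure. This is more than condensed detail, because the article names the covariate and its most natural reading would bias a primary objective.

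If the final volume is used, the total effect of continuing is not recovered whenever continuing changes bleeding in either direction: harm is hidden if it adds bleeding, benefit is hidden if it reduces it. The illustrated errors of about 8 points for a shift of half a standard deviation rest wholly on assumed parameters and show only that the problem need not be small. The documents fix neither the direction nor the size.

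**What to change.** In aim 5, replace the extravasation amount with severity known at the continue/abort decision: the first-run flow rate and perforation location already used in aim 4, plus extravasation visible on runs up to the decision. State that all other propensity covariates are limited to variables settled before the decision. Keep postinterventional hemorrhage volume as an outcome only. If flow rate was meant all along, saying so resolves the main point.

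The cost is a sentence or two in the analysis plan. The core laboratory already plans to read the first run showing extravasation, and no further patients are needed. The small downside is that severity at the decision is measured less precisely than final volume, so some residual confounding may remain.
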